### Strategies to improve adherence to interventions {11c}

To promote participant retention, travel to the hospital can be organized by the investigators and financially compensated (e.g. costs for a taxi). While the beneficial effects of rTMS remain to be demonstrated, we expect a higher degree of resection with the preservation of motor function in the active rTMS arm. In addition, a closer patient connection through daily study participation can positively influence patients’ fear of surgery and mood. The flexible treatment duration tailors to individual patient’s needs and changes in treatment schedules without affecting the completeness of study parameters. Therefore, we expect a high level of compliance on the patients’ side.

### Relevant concomitant care permitted or prohibited during the trial {11d}

No restrictions apply with respect to patients’ medication before or during the trial and treatments before the trial. During the trial, treatment with additional therapeutic brain stimulation methods is not permitted as this would impact the outcome assessment.

### Provisions for post-trial care {30}

No special treatment is planned for patients completing the trial. Patients will receive their treatments and clinical follow-ups according to the standard of care as determined by the treating neurosurgeon. Any patients suffering harm from trial participation will receive the standard treatment for the symptoms they have been experiencing by the medical staff of the respective hospital.

### Outcomes {12}

#### Primary endpoints

The BMRC score for upper extremities will be measured 3 months postoperatively. The BMRC score is scored on a 5-point scale, where 0 corresponds to no muscle contraction in assessed muscles and 5 to normal muscle strength [17]. It has been used in various nTMS studies in brain tumor patients to quantify motor impairment [13, 18]. Furthermore, preservation of function is one of the most important factors influencing quality of life after surgery.

The gross total resection rate (GTR) is additionally measured 7 days postoperatively as one of the most important prognostic markers for the survival of patients. A lower residual tumor volume directly correlates with an improved survival of a patient [3]. The resection success is manually measured by an external neuroradiologist (not part of the study) on a postoperative structural MRI (acquired as part of the clinical routine commonly on the first to third postoperative day). If no residual tumor is detectable, the resection is classified as a gross total resection (binary: yes/no). To aid this assessment, preoperative MRIs can be used for comparison.

#### Secondary endpoints

Health-related quality of life will be measured with the EORTC QLQ-BN20 as an important patient-oriented outcome 7 days and 3 months after surgery. The questionnaire results in a numerical value between 0 and 100, with 100 representing the worst possible score. Therefore, all single-item scores are summed and analyzed using a standard formula as described in the scoring manual [19]. The questionnaire is designed and validated to measure health-related quality of life in brain tumor patients [19].

Functional connectivity in resting-state functional magnetic resonance imaging (fMRI) will be used as a marker for functional reorganization after the intervention (T1) and to give insights into which networks are recruited to compensate for imminent functional loss [20]. Functional connectivity is evaluated in resting-state fMRIs using a seed-to-voxel approach with the seed placed on the stimulated primary motor cortex region. Preprocessing is carried out using fMRIprep [21]. Seed-based connectivity is then quantified as Fisher-transformed correlation coefficients between the motor cortex blood oxygenation level-dependent (BOLD) time series and each individual voxel BOLD time series.

The Action Research Arm Test (ARAT; [22, 23]) is a 19-item observational measure of upper extremity performance. It specifically tests motor performance with respect to four subscales: grasp, grip, pinch, and gross movement. Each task on the ARAT is scored between 0 (patient can perform no part of the test) and 3 (patient performs test normally) [22, 23]. Individual task scores are summed up leading to an overall test score between 0 (worst) and 57 (best score). While the test has not been specifically validated for use in brain tumor patients, it is intensively used in stroke, multiple sclerosis, brain injury, and Parkinson’s disease patients. In these populations, it has proven good reliability and validity and is often used physiotherapists to assess treatment progress.

### Participant timeline {13}

The study is planned to run from March 2023 until July 2025, with recruitment starting in October 2023 in both recruitment centers. Participants are recruited from the regular incoming patients via advertisements, ambulatory care, or the in-patient ward. They will undergo MRI imaging, a clinical assessment, and nTMS assessment as part of the clinical routine. Following these screening procedures, eligible patients will be invited to participate in the study and randomized. The rnTMS intervention will be applied for 5–28 days twice daily, depending on the individually available presurgical time. Each rnTMS session is followed by a short motor training. Ideally on the day following the last rnTMS session, depending on the surgical schedule, patients will undergo resection of the tumor. Follow-up measurements are scheduled immediately after the rnTMS intervention (T1), 7 days postoperatively (T2), and 3 months postoperatively (T3). Table 1 gives an overview of study visits and timepoints as well as the procedures performed per timepoint.

**Table 1 Tab1:** Participant timeline

**Study procedure**	**Screening**	**Baseline**	**Intervention**	**After intervention**	**Surgery**	**7 days post-operative**	**3 months post-operative**
Visit number		T0		T1		T2	T3
Study day	−1	0	0–5/28	5/28	6/29	13/36	3 months
Informed consent	X						
Inclusion/exclusion criteria	X						
Demographics, medical/neurol. history	X						
nTMS measurement	X			X			
Motor status (BMRC)^a^		X		X		X	X^a^
Structural MRI incl. assessment of GTR^a^	X			X		X^a^	
EORTC-BN20		X		X		X	X
ARAT		X		X		X	X
Diffusion-weighted MRI	X						
Resting-state fMRI	X			X			
rnTMS stimulation			X				
Motor training			X				
(Serious) adverse events^b^		X	X	X	X	X	X
Details of surgery					X		
Tumor histology						X	

Depending on the individually available time before surgery, patients enrolled in the study can have varying treatment durations (5–28 days) and thus, complete their study visits on different study days. The first follow-up measurement (T1) is always performed immediately after the intervention and before surgery. The surgery is then performed on the day after the last treatment, that is, the earliest on study day 6 or the latest on study day 29. Postoperative follow-ups are performed 7 days (T2) and 3 months (T3) after surgery, i.e. the earliest on study day 13 and the latest on study day 36 for T2 and respectively 3 months later for T3

^a^The motor status (BMRC) at T3 and gross total resection rate at T2 are measured as primary endpoints

^b^(Serious) adverse events will be monitored continuously throughout the trial

### Sample size {14}

This is the first study to our knowledge showing the safety and efficacy of rnTMS in glioma patients with regard to postoperative motor status and GTR.

#### Motor status

Data from a small study by Ille et al. (*n* = 19; [11]) demonstrate high effect sizes of 1.66 for the Fugl-Meyer Assessment (FMA) at 3 months follow up in rnTMS compared to sham (mean change in FMA: 31.9 (standard deviation (SD): 18.4) in rnTMS compared to 4.2 (SD: 10.4) in sham, common SD: 16.7). In a meta-analysis combining 10 study estimates for low-frequency rTMS compared to controls in stroke patients, Hsu et al. [24] reported an effect size of 0.69 (95% CI: 0.42–0.95) regarding motor function outcomes. In our study, we aim to demonstrate non-inferiority of motor status at T3 in the rnTMS group compared to sham using the BMRC score (ordinal values between 0 and 5). We use a non-inferiority margin of 0.5 points (difference of group medians), corresponding to the probability of a worse outcome in the intervention group compared to in the control group of *P*(*x* > *y*) = 55.0% (assuming a mean difference of 0.5 and common standard deviation of 2.5, corresponding to an odds ratio (OR) of 1.35 [15], or Cohen’s *d* of 0.17 [16]). We will show that the OR for a worse outcome in the intervention compared to the sham group is significantly below 1.35 (one-sided significance level *α* = 0.025) using 66 sham patients and 66 rnTMS patients. This is possible if the true OR is at least 0.74 (95% CI: 0.23–1.25) (corresponding to a Mann-Whitney measure of P(x > y) = 45.0%, or Cohen’s *d* of − 0.17). This sample size calculation is based on a simplified dichotomous measure, not an ordinal measure, using a similar effect size for an OR of two proportions (50.0% vs. 42,4%, nQuery Advisor 8): When the sample size is 132 (with group 1 and 2 sample sizes of 66 and 66), a one-sided (upper) 97.5% confidence interval for the odds ratio of two proportions will range from the sample proportion odds ratio of 0.74 to an upper limit of 1.24, assuming a worse outcome in 42.4% of patients in the intervention group and in 50.0% of patients in the control group. The confidence interval was calculated using the Simple Asymptotic Method. While we analyze the primary outcome in an ordinal regression model, we expect a similar effect estimate. We demonstrate this at a one-sided significance level of *α* = 0.025 with a power of 80%. Additionally, in case of a 95% CI of the OR for a worse outcome below 1 in the intervention compared to the control we can demonstrate superiority of the intervention.

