### Objectives {7}

#### Primary hypotheses

We hypothesize that preoperative rnTMS can induce a functional reorganization of the stimulated motor network, leading to (a) a comparable or better motor status (British Medical Research Council (BMRC) score for upper extremities) 3 months postoperatively (T3) (non-inferiority), and (b) a higher gross total resection rate (superiority) in the rnTMS group compared to the sham group.

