## Statistical methods

### Statistical methods for primary and secondary outcomes {20a}

#### Efficacy

To test both main hypotheses of comparable motor status at T3 and a higher GTR in rnTMS patients compared to sham patients, we will apply hierarchical testing at a two-sided significance level of *α* = 0.05 (Power = 80%). Primary hypotheses will be tested in an intention-to-treat (ITT) framework using multiple imputed datasets in case of missing values (under the assumption of MCAR or MAR) after a single imputation of informative missing values (MNAR) for example for patients with worsened health status or patients who die during follow up.

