#### Description of the primary efficacy analysis and population

(1) Non-inferiority of motor status at T3 in the rnTMS group vs. sham group will be tested using an ordinal regression model (adjusted for baseline motor status) with dependent variable motor status at T3 (ordinal: six categories). Additionally, center, duration of rnTMS/sham training, and age will be included as covariates. Non-inferiority is successfully proven, if the upper limit of the 95% CI of the odds ratio for a worse outcome in the intervention group is below 1.35 according to the pre-specified non-inferiority margin. (2) The second main hypothesis, that the GTR is higher in the rnTMS compared to the sham group, will be tested (only if the first hypothesis has been proven, hierarchical testing) at a two-sided significance level of *α* = 0.05 using a binary logistic regression model with gross total resection (yes/no) as a dependent variable, group allocation, center, duration of rnTMS/sham training, and age as independent variables. A per-protocol analysis will be conducted as a sensitivity analysis.

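### The 80% power for motor non-inferiority is not what 66 per arm delivers: about 30–50% at the assumed OR of 0.74 and about 11–16% at equality, and *at least 0.74* should read *at most 0.74*

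*Protocol article*

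**What the plan says.** The first primary hypothesis (Objectives {7}) is "a comparable or better motor status (British Medical Research Council (BMRC) score for upper extremities) 3 months postoperatively (T3) (non-inferiority"). The decision rule (Statistical methods {20a}, primary efficacy analysis) declares non-inferiority "if the upper limit of the 95% CI of the odds ratio for a worse outcome in the intervention group is below 1.35". GTR is tested second, and only if the first hypothesis has been proven.

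The power statement is in Sample size {14}, Motor status. It reads "This is possible if the true OR is at least 0.74" (printed 95% CI 0.23 to 1.25), with 66 patients per arm. It uses a dichotomous stand-in for the ordinal score, "assuming a worse outcome in 42.4% of patients in the intervention group and in 50.0% of patients in the control group", and says that "a one-sided (upper) 97.5% confidence interval for the odds ratio of two proportions" will run from 0.74 to 1.24. It then claims to demonstrate this "with a power of 80" per cent.

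The Efficacy paragraph opens "To test both main hypotheses of comparable motor status at T3 and a higher GTR in rnTMS patients compared to sham patients" and gives 80% power for the hierarchical procedure. It does not say which true OR the figure refers to.

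**The concern.** Three things do not fit together.

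- **Direction.** For an OR of a worse outcome that must be shown to lie below 1.35, a larger true OR lowers the chance of success. Read literally, *at least 0.74* covers 1.0 and above.
- **Scenario.** The Efficacy paragraph places 80% beside comparable motor status, but the only calculation behind it assumes that rnTMS is better. No figure is given for equality.
- **Method.** An expected confidence limit below the margin does not give 80% power. If the expected limit sat exactly on the margin, power would be about 50%.

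The hierarchy is what is at stake. If motor status is preserved and resection improves, GTR can be tested formally only when the first test passes. The chance of that is much lower than the text suggests.

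**Working it through.** **Inputs from the protocol.** n = 66 per arm; margin OR 1.35; one-sided 0.025 (z = 1.96); worse outcome 42.4% (rnTMS) vs 50.0% (sham); planned analysis is ordinal regression with six categories. **Assumption not in the protocol:** the distribution of BMRC scores at 3 months, varied below.

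**1. The plan's own interval.**
- OR = (0.424/0.576)/(0.5/0.5) = 0.736.
- SE(log OR) = √[1/(66·0.424·0.576) + 1/(66·0.5·0.5)] = 0.350.
- Untransformed scale: SE = 0.736 × 0.350 = 0.258, and 0.736 ± 1.96 × 0.258 = 0.23 to 1.24. This reproduces the printed limits.
- Log scale: exp(ln 0.736 ± 1.96 × 0.350) = 0.37 to 1.46. The upper limit is above 1.35.

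**2. Power at the assumed benefit.** Power = Φ[(ln 1.35 − ln OR)/SE − 1.96].
- Binary, log scale, OR 0.736: Φ(−0.228) = 41%; at exactly 0.74 it is 40%. Exact binomial enumeration of the 42.4% vs 50.0% case gives 39.8%.
- Untransformed scale: Φ[(1.35 − 0.736)/0.258 − 1.96] = 66%; exact enumeration 60.5%.
- 80% on the binary log scale needs a true OR of about 0.49 (33% vs 50%).

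**3. Power at true OR = 1 (50% vs 50%).**
- SE = √[2/(66·0.25)] = 0.348.
- Log scale: Φ(ln 1.35/0.348 − 1.96) = 13.6%; exact 12.9%.
- Plan's raw-scale interval, exact: 27.1%.
- An observed OR of exactly 1.0 fails either way. The raw upper limit is 1 + 1.96 × 0.348 = 1.68. With this SE, the largest observed OR that passes is 1.35/1.68 = 0.80 on the raw scale, and exp(ln 1.35 − 1.96 × 0.348) = 0.68 on the log scale.

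**4. The planned ordinal model.** Proportional-odds approximation: SE = √[12/(132(1 − Σp³))], where p are the category proportions averaged over both arms. Sham-arm distributions from score 0 to 5:

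| Assumed distribution (%) | Power at OR 1 | Power at OR 0.74 |
|---|---|---|
| uniform | 16.4% | 50% |
| 5, 5, 5, 10, 25, 50 | 15.0% | 44% |
| 1, 1, 2, 6, 20, 70 | 12.3% | 34% |
| 1, 1, 2, 4, 14, 78 | 10.7% | 28% |

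Simulation (1,500 runs each) gave 17.1% and 47.9% for the uniform case, and 14.0% and 40.9% with half at the top score. A baseline-adjusted ordinal model (500 runs, OR 1, about 72% at the top score) gave 12.6%.

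**5. Sensitivity to n.** If all 148 patients counted in full (74 per arm), power would be 14.7% (binary, log scale) to 17.7% (ordinal, uniform) at OR 1, and 44% to 54% at OR 0.74.

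**6. The GTR figure.** 74% vs 50% with 66 per arm gives 81.8%, matching the stated 82%. It is the power of that test once it is reached.

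**The case against.** The strongest reply is that nothing is hidden. Powering a non-inferiority test on an expected benefit is legitimate. The protocol states the assumed OR, the matching Mann-Whitney probability of 45.0% and the Cohen's d of −0.17, after citing prior effect sizes of 1.66 and 0.69. The hypothesis is comparable or better, and the Efficacy paragraph may simply abbreviate it. The figures beside *at least 0.74* show that a benefit was meant, perhaps as *at least this favourable*, and the decision rule itself is correct. The trial is described as exploratory phase 2b, and effect estimates with 95% intervals are already promised for each primary and secondary analysis.

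Most of this stands. A reader might infer that the protocol explicitly claims 80% power at OR = 1. It does not, because the Efficacy paragraph gives no separate calculation. A reader might also infer that the design almost never succeeds at equality. That is too strong, given 11–16%, or 27% by the only interval method the protocol names. That a failed test would be taken as motor harm is a risk, not something the documents imply.

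The reply does not rescue the 80%. That figure is not reached at the disclosed OR of 0.74 on either scale.

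**Conclusion.** The point holds as an error in the stated power and in one word of the sample size section. At the assumed OR of 0.74, the chance of showing non-inferiority is about 40% (binary, log scale), about 30–50% (ordinal) or 61–66% (raw scale). At equality it is about 11–16% on the log-OR scale, or 27% on the raw scale. If motor status is truly equal, GTR would therefore go formally untested in about 84–89% of trials, or 73% with the raw-scale interval.

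The ordinal figures rest on proportional odds and on an assumed score distribution, from uniform to about 78% at the top score. No variant tried reaches 80% at 0.74.

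Two further readings are tempting. One is that 80% is right provided the true OR is 0.74 or lower; the plan's own inputs contradict this at 0.74. The other is that the margin, the test or the sample size must be changed. The documents do not require that, because the benefit assumption is legitimate and the trial is presented as exploratory. What must change is what the protocol says the design can show.

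**What to change.** 1. Sample size {14}, Motor status: change *at least 0.74* to *at most 0.74*.
2. In the same section and in Efficacy, replace the unqualified 80% for motor status with the power at named true ORs under the planned ordinal model, with the assumed score distribution stated. On the present figures that is about 30–50% at 0.74 and about 11–16% at 1.0. Do not state or imply that 80% holds at 0.74. Describe the 1.24 as an expected limit on the untransformed scale, not as a power result.
3. Sample size {14}, GTR: add that the 82% is conditional on the motor test having passed.
4. Primary efficacy analysis: add that an upper limit above 1.35 with an OR near 1 is inconclusive, and that GTR is then reported as an estimate with 95% CI and without a confirmatory claim. The estimate is already promised; the new part is the interpretation.

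The cost is wording and one recalculation. The published power becomes less favourable. Patients, margin, test and sample size are unaffected.

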## Introduction

### Background and rationale {6a}

Around 8300 cancers of the central nervous system and 6140 deaths are reported in Germany every year [1]. These cancers are associated with 150,993 disability-adjusted life years reported in 2016 [1]. Furthermore, an increase in sick leave is observed in these patients before surgery with a return-to-work rate of only 50% 1 year after surgery [2], thus presenting a major socioeconomic burden. While maximal surgical resection has been linked with improved overall survival, up to 50% of intrinsic brain tumors are not completely resected due to infiltration of functional brain tissue. In addition, up to 25% of patients with brain tumors in motor areas suffer from new or worsened motor deficits postoperatively. Both, incomplete tumor resection and impaired neurological status, are directly correlated with decreased life expectancy [3, 4]. While surgical resection is the most effective treatment option for intrinsic brain tumors, traditionally, tumors that have been demonstrated to infiltrate functional tissue will be diagnosed as inoperable and will be treated conservatively from then on. However, in recent years the concept of neurological functions being confined to specific areas of the brain has been questioned and a novel concept of function being represented in dynamic cortico-subcortical networks has been introduced [5]. This paradigm shift also implies that function can move, for example, due to the presence of a pathology — yet typically, the reshaping is too slow or ineffective to sustainably affect the clinical course of the patient.

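### The stated 80% power for non-inferiority of motor status does not follow from the sample size calculation: at its own inputs the log-scale upper limit is 1.46, not 1.24, and power is about 41%

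*Protocol article*

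**What the plan says.** The section Sample size {14}, Motor status, replaces the ordinal outcome by a dichotomous one, "assuming a worse outcome in 42.4% of patients in the intervention group and in 50.0% of patients in the control group", with 66 patients per arm. It reports "a one-sided (upper) 97.5% confidence interval for the odds ratio of two proportions", which "will range from the sample proportion odds ratio of 0.74 to an upper limit of 1.24", and adds: "The confidence interval was calculated using the Simple Asymptotic Method". Earlier in the same paragraph the effect is introduced with "This is possible if the true OR is at least 0.74 (95% CI: 0.23–1.25". The paragraph then claims that non-inferiority is shown at a one-sided level of 0.025 "with a power of 80" per cent. The 80% is repeated under Efficacy in section {20a}.

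The planned test is in Description of the primary efficacy analysis and population. An ordinal regression on six BMRC grades, adjusted for baseline motor status, center, duration and age, shows non-inferiority "if the upper limit of the 95% CI of the odds ratio for a worse outcome in the intervention group is below 1.35". Gross total resection (GTR) is tested only if that step succeeds.

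**The concern.** The printed interval of 0.23 to 1.25 is symmetric about 0.74 (0.51 on each side). An interval obtained by exponentiating a log odds ratio is not symmetric on that scale, so the calculation does not seem to describe the interval that the planned regression would normally produce. In addition, the paragraph goes from where the upper limit falls when the estimate equals its expected value directly to a power of 80%, with no step between.

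Non-inferiority of motor status is the first step of the hierarchy. The chance of a formal claim on GTR, for which the article states 82% power, cannot exceed the chance of passing this first step. If the 80% is wrong, readers are misled about both primary hypotheses.

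**Working it through.** **Inputs, all from the Motor status paragraph:** worse outcome in 42.4% (rnTMS) and 50.0% (sham); 66 per arm; margin 1.35; one-sided alpha 0.025.

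**1. Odds ratio and standard error**
- OR = (0.424/0.576)/(0.500/0.500) = 0.736; ln OR = −0.306.
- SE(ln OR) = √[1/(66 × 0.424 × 0.576) + 1/(66 × 0.5 × 0.5)] = 0.350.

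**2. Reproducing the printed limits**
- Raw scale: 0.736 ± 1.96 × 0.736 × 0.350 = 0.231 to 1.241. This is the printed 1.24.
- The same with 0.74 as the centre: 0.232 to 1.248. This is the printed 0.23–1.25.

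**3. The interval on the log-odds scale**
- exp(−0.306 ± 1.96 × 0.350) = 0.37 to 1.46. The expected upper limit exceeds 1.35.

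**4. Power at the stated inputs**
- Log scale: Φ[ln(1.35/0.736)/0.350 − 1.96] = Φ(1.732 − 1.96) = 41%. Exact binomial enumeration of the same rule gives 40%.
- Raw scale: Φ[(1.35 − 0.736)/(0.736 × 0.350) − 1.96] = Φ(2.381 − 1.96) = 66%. Exact enumeration gives 61%. At a true OR of 1.35 with a 50% control rate, this rule has a one-sided type I error of about 7% against the nominal 2.5%, so adopting the raw-scale interval is no remedy.

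**5. Why a limit below the margin is not 80% power**
- If the expected upper limit equals the margin, power is about 50%.
- For 80% it must lie a further 0.84 standard errors below the margin. On the raw scale that is 1.35 − 0.84 × 0.258 = 1.13. On the log scale it is exp(0.300 − 0.84 × 0.350) = 1.01. The printed 1.24 misses even the first.

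**6. Unadjusted ordinal model**
- Under proportional odds, the information is about (N/12)(1 − Σp³), where p are the proportions in each grade. It cannot exceed N/12.
- N = 132: SE ≥ √(12/132) = 0.302; power ≤ Φ(0.606/0.302 − 1.96) = 52%.
- N = 148: SE ≥ √(12/148) = 0.285; power ≤ Φ(0.606/0.285 − 1.96) = 57%.
- With 132 patients, six equally filled grades give about 50%. If 70% of patients were at grade 5 (an assumption), it would be about 36%.

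**7. Adjusted ordinal model (assumed scenarios only)**
- The article gives neither a BMRC distribution nor a baseline correlation. Over a set of assumed values, power was mostly about 35–65%. The extremes were 29% (70% at grade 5, 0.74 taken as the conditional OR) and 71% (equal grades, 60% of latent variance explained by baseline, 0.74 taken as the marginal OR). None reached 80%.

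**8. What 132 patients can show with 80% power**
- Dichotomous, control 50%, with the SE recomputed as the intervention rate changes: OR 0.493 (intervention rate 33.0%, SE 0.359). Check: ln(1.35/0.493)/0.359 = 2.80 = 1.96 + 0.84.
- Unadjusted ordinal: exp(0.300 − 2.80 × SE) gives 0.57 for equal grades (SE 0.306) and 0.53 if 55% were at grade 5 (SE 0.334, an assumption).
- Conversely, 80% power at the stated rates needs about 173 per arm on the log scale.

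**The case against.** The strongest reply is that the dichotomous calculation is openly labelled a simplification and that the planned test is an adjusted ordinal model. That is right, and it means the 41% belongs to the printed calculation. A reader might take it as the power of the planned analysis; the documents do not support that, because the gain from baseline adjustment cannot be fixed without figures the article does not give. The reply does not restore the 80%: the unadjusted ordinal model cannot reach it, and no assumed adjusted scenario did.

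Second, 132 is pessimistic. The article expects about 2% missing BMRC scores, sets deaths to the worst value and imputes the rest, so close to 148 may be analysed. This helps a little: at most 57% for the unadjusted ordinal model.

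Third, 0.74 may be a cautious planning value. The stroke meta-analysis cited in the same section gives an effect size of 0.69 with a lower bound of 0.42. Converted by exp(−0.42 × π/√3), the lower bound is an OR of 0.47, for which dichotomous log-scale power is about 84%. The low power is therefore conditional on OR 0.74. For this reason, the inference that the trial is more likely than not to fail is not supported: the adjusted scenarios straddle 50%, and the true effect may be larger.

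A reader might also lower the power further by using the background statement that "up to 25% of patients with brain tumors in motor areas suffer from new or worsened motor deficits postoperatively" as the control rate. That figure describes new or worsened deficits, whereas the 50.0% is a stand-in for an ordinal comparison. The two are not interchangeable.

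Finally, the Discussion calls the trial an exploratory phase 2b study. That softens the consequence but does not make a stated power figure correct.

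**Conclusion.** The concern holds. The stated 80% cannot be obtained from the stated inputs, either on the log-odds scale (about 41%) or with the raw-scale interval actually used (61–66%). The expected 95% interval for the dichotomous calculation is 0.37 to 1.46, so the upper limit is above the margin. These figures need only the printed rates, arm sizes and margin, and the usual practice of forming regression intervals on the log-odds scale.

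For the planned adjusted ordinal model, the supportable statement is that power at OR 0.74 is clearly below 80% in every scenario examined. Its exact value rests on assumptions about grade distribution and baseline correlation. The shortfall carries over to GTR through the hierarchy.

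The phrase about a true OR of at least 0.74 is a minor wording fault. It presumably means an effect at least that strong, but because the odds ratio is for a worse outcome, larger values make non-inferiority harder. No calculation depends on it.

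**What to change.** - In Sample size {14}, Motor status, replace the raw-scale calculation by the log-scale one: 95% interval 0.37–1.46, expected upper limit 1.46, power about 41% on the dichotomous basis.
- If power for the ordinal model is quoted, give it with the assumed BMRC distribution and baseline correlation labelled as assumptions.
- State the true OR at which 132 patients give 80% power: about 0.49 on the dichotomous basis, and about 0.53–0.57 for the unadjusted ordinal model under assumed grade distributions.
- Correct the 80% under Efficacy in section {20a}.
- Change the wording on the true OR from at least 0.74 to at most 0.74.

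The cost is a rewrite of one paragraph, one correction in the methods and matching text in the analysis plan. The stated power becomes less favourable. No extra patients or procedures are needed.
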